## Abstract

**Background:**

Some studies have suggested an association between omega-3 long-chain polyunsaturated fatty acids (*n*-3 LC PUFAs) and better cognitive outcomes in older adults. To date, only two randomised, controlled trials have assessed the effect of *n*-3 LC PUFA supplementation on cognitive function in older cognitively healthy populations. Of these trials only one found a benefit, in the subgroup carrying the ApoE-ε4 allele. The benefits of *n*-3 LC PUFA supplementation on cognitive function in older normal populations thus still remain unclear. The main objective of the current study was to provide a comprehensive assessment of the potential of *n*-3 LC PUFAs to slow cognitive decline in normal elderly people, and included ApoE-ε4 allele carriage as a potential moderating factor. The detailed methodology of the trial is reported herein.

**Methods:**

The study was a parallel, 18-month, randomised, double-blind, placebo-controlled intervention with assessment at baseline and repeated 6-monthly. Participants (N = 391, 53.7% female) aged 65-90 years, English-speaking and with normal cognitive function, were recruited from metropolitan Adelaide, South Australia. Participants in the intervention arm received capsules containing fish-oil at a daily dosage of 1720 mg of docosahexaenoic acid and 600 mg of eicosapentaenoic acid while the placebo arm received the equivalent amount of olive oil in their capsules. The primary outcome is rate of change in cognitive performance, as measured by latent variables for the cognitive constructs (encompassing Reasoning, Working Memory, Short-term Memory, Retrieval Fluency, Inhibition, Simple and Choice-Reaction Time, Perceptual Speed, Odd-man-out Reaction Time, Speed of Memory Scanning, and Psychomotor Speed) and assessed by latent growth curve modeling. Secondary outcomes are change in the Mini-mental State Examination, functional capacity and well-being (including health status, depression, mood, and self-report cognitive functioning), blood pressure, and biomarkers of *n*-3 LC PUFA status, glucose, lipid metabolism, inflammation, oxidative stress, and DNA damage.

**Trial registration:**

Australia and New Zealand Clinical Trials Register (ANZCTR): ACTRN12607000278437

## Background

Ageing is accompanied by what is normally considered to be inevitable cognitive decline, although the extent to which this occurs is highly variable, and strongly affected by various disease processes. Cognitive function is a major determinant of quality of life in older age and decline in cognitive functioning is a primary contributing factor to increasing dependency in the elderly. Due to the ageing profile of the population, the financial, social, and other burdens that this dependency places upon society are of increasing concern. Thus, finding ways to prevent or ameliorate age-related cognitive decline is a public health imperative, with potential benefits not just in terms of lessening aged care costs but also in the enhancement of well-being in a growing segment of society.

Omega-3 polyunsaturated fatty acids (*n*-3 PUFAs) are one diet-related factor suggested to influence cognitive decline during ageing. The *n*-3 long-chain (LC) PUFAs eicosapentaenoic acid (EPA) and docosahexaenoic acid (DHA) are crucial to brain development and normal brain functioning [1]. DHA is particularly important to brain functioning due to its influence on neural membrane properties, which modulate cell signalling [2]. DHA concentration in the brain decreases with age in humans [3] and rats [4]; this has been postulated to be consequential to the age-related deterioration in central nervous system functions [3]. Evidence from animal studies supports this; animals fed a low *n*-3 PUFA diet show cognitive deficits [4,5] that are ameliorated by DHA supplementation [6,7] and DHA supplementation improves memory performance in aged mice [8].

### Cross-sectional and prospective studies

Oily fish are the major dietary source of the *n*-3 LC PUFAs, EPA and DHA. A consistent finding across studies is that higher intake of fish is related to less cognitive decline [9-12] and incidence of dementia [10,13,14] in prospective studies, and associated with better cognitive performance in non-clinical samples [11,15-17], in cross-sectional analyses. However, variable associations have been found between dietary intake levels of *n*-3 LC PUFAs and cognitive outcomes; only a handful of the aforementioned studies that also examined relationships between cognitive outcomes and dietary intake levels of *n*-3 LC PUFAs have found significant positive relationships [9,14,15].

Stronger evidence of a positive relationship between cognitive outcomes in older age and levels of *n*-3 LC PUFAs has been found in studies assessing plasma or erythrocyte levels of *n*-3 PUFAs. In these studies, DHA and EPA levels, either individually or in combination, have been associated with better cognitive function in normal older adults in cross-sectional analyses [18,19], and in prospective studies, with better cognitive outcomes over time [19] or reduced risk of cognitive decline [20], and lower risk of developing dementia [21]; in contrast, Laurin et al [22] reported a negative relationship between cognition and biomarkers of *n*-3 LC PUFAs.

### Randomised controlled trials (RCTs)

There have been six published double-blind RCTs of *n*-3 LC PUFAs on cognitive functioning in the elderly within both clinical and non-clinical populations [23-28]. Only two studies have been conducted with cognitively healthy populations, screened for dementia at baseline, and no overall effect of supplementation was found. The "Older People and *n*-3 Long-chain polyunsaturated fatty acids" study [24] supplemented 867 cognitively healthy participants aged 70-79 years, with either 200 mg of EPA and 500 mg of DHA, or olive oil, daily for 24 months. After adjustment for confounders, there was no significant difference between the groups in performance on the California Verbal Learning Test, the main cognitive outcome measure, or any secondary cognitive outcomes (a global cognitive score, and domain scores on memory, processing speed, executive function, and delayed recall). In a 26-week RCT of fish oil on cognitive performance in 302 cognitively healthy adults aged 65+ years [27], no main effect of supplementation was seen for any of the cognitive domains (attention, sensorimotor speed, memory, and executive function), assessed by 5 tests. However, subgroup analysis revealed that carriers of the Apolipoprotein E (ApoE) ε4 allele, in both the low (226 mg EPA, 176 mg DHA) and high dose (1093 mg EPA, 847 mg DHA) fish oil groups, showed an improvement after 26 weeks compared with the placebo on the Digit-Span Forward task, their marker of attention.

In three of the studies with cognitively impaired (including Alzheimer's disease (AD)) samples, the interventions had a beneficial effect on cognitive outcomes but only in participants with mild cognitive dysfunction [23,25,28]. This finding was not replicated in a large RCT conducted over 18 months of 402 participants with mild to moderate AD. However, in this study in ApoE-ε4 non-carriers only, there was a positive effect on two cognitive outcome measures [26].

### Apolipoprotein E-ε4 allele

The presence or absence of the Apolipoprotein E-ε4 allele appears to be a potentially important modifier of relationships between *n*-3 LC PUFAs and older-age cognitive outcomes but there are conflicting findings regarding the direction of this interaction. Epidemiological studies that have reported a differential relationship between cognitive outcomes and measures of *n*-3 LC PUFAs for carriers versus non-carriers of the ApoE-ε4 allele have found a beneficial relationship present only in non-carriers [19,29]. However, the two RCTs that have included examination of the effect of ApoE-ε4 allele carriage in sub-analyses have reported a beneficial effect of supplementation dependent on ApoE-ε4 allele status, but differ on which group benefits from supplementation [26,27]. Nonetheless, ApoE polymorphisms have been found to influence lipid responses to fish oil supplementation [30] and in a small group of males, those without ApoE-ε4 showed a greater increase in DHA and EPA after fish-oil supplementation [31]. Further, possession of the ApoE-ε4 allele is associated with worse cognitive performance in old age [32] and greater risk of cognitive decline and dementia [33], hence, even in cognitively healthy samples screened for dementia, the genesis of any cognitive change may differ between carriers and non-carriers, providing another potential avenue for differential effects of supplementation on cognitive outcomes due to ApoE genotype.

These studies suggest that *n*-3 LC PUFA intake, in particular DHA, has a beneficial effect on cognition in older adults. However, the majority of evidence for the benefits of *n*-3 PUFA on cognitive functioning in adults is associational. Furthermore, work to date in this area has often not comprehensively assessed cognitive function or cognitive decline. Without *a priori *expectations of specific cognitive domains that will be affected, a comprehensive operationalisation of cognition is required in order to ascertain whether a null result is due to the absence of a relationship or effect, or the relevant cognitive domains were not assessed. Given the potential importance of ApoE-ε4 allele carriage as a determinant of *n*-3 LC PUFAs influence upon cognitive outcomes in older age, more randomised controlled trials are needed that incorporate consideration of its impact in order to determine whether *n*-3 LC PUFAs can influence age-related cognitive change in older adults.

## Methods/Design

The primary aim of the current trial was to comprehensively assess over 18-months the efficacy of a DHA-rich fish-oil supplement on slowing cognitive decline in non-demented older adults; the hypothesis was that, over 18 months, the *n*-3 LC PUFA supplementation group would show slower cognitive decline than the control group. The trial was set within the broader context of examining nutritional, health, and lifestyle factors associated with better cognitive and well-being outcomes in the elderly, both cross-sectionally and longitudinally.

Secondary aims were: 1) to explore relationships between measures of *n*-3 LC PUFA intake and measures of cognitive function at baseline; 2) to determine whether the effect of *n*-3 LC PUFA supplementation on cognitive decline is moderated by presence of the ApoE-ε4 allele, initial cognitive status, measures of dietary *n*-3 LC PUFA intake (including changes in *n*-3 LC PUFA status) or any nutritional, health-related, or psychological factors associated with cognitive outcomes in the elderly; 3) to examine the effect of the intervention on measures of functional capacity and well-being; and 4) examine relationships between measures of *n*-3 LC PUFA intake and functional capacity and well-being at baseline.

This paper details the methodology of the study, including the design, assessment battery, and research protocols used.

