#### Compliance

Compliance was monitored via a count of all unused supplements returned at three-monthly intervals, along with self-report calendars, mailed back on a monthly basis throughout the trial. If participants' compliance fell below 85% on the basis of their calendars, they were contacted by a research officer who noted the reasons. Compliance also will be assessed by examination of erythrocyte membrane *n-*3 LC PUFA status and changes in status, via a blood sample taken at every 6 month-assessment.

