For each assessment visit, participants attended the clinic after an overnight fast, and a blood sample and physical measurements (height (at baseline only), weight, and blood pressure) were undertaken by trained phlebotomists and staff. Participants were then given a standardised breakfast in the centre, prior to undertaking the cognitive test battery. At baseline and final assessment, blood was taken for measurement of the following. Carotenoids, folate, and vitamin B12, were assessed, all having been associated with cognitive functioning in the elderly; this enables examination of cross-sectional associations between these measures and outcomes, and if necessary in the intervention analyses, to control for any potential differences between groups at baseline or any changes in these measures that differ between groups (despite randomisation). Glucose, glycated haemoglobin (HbA1c), lipid concentrations (total cholesterol, high-density lipoprotein (HDL), low-density lipoprotein (LDL), and triglycerides), and homocysteine were also measured at baseline and final assessment, because of associations between abnormalities in these parameters of metabolism and cognitive dysfunction [30]. Inclusion of these measures allows us to control for possible baseline differences between groups and potentially assess whether any changes on these measures due to the intervention mediate changes on the main outcome variables. Finally, our blood-derived measures included a high sensitivity assay for C-reactive protein (CRP), an inflammatory marker, plasma malondialdehyde (MDA), a marker of oxidative stress, and telomere length, a marker of oxidative stress and DNA damage. Oxidative stress and inflammation have been associated with cognitive decline or impairment [40,41] and are two postulated mechanisms through which *n*-3 LC PUFAs may exert an effect on cognitive functioning [34,35]; thus, we will examine cross-sectional associations between these measures and our cognitive outcomes, be able to control for potential differences between groups at baseline, and assess whether any changes due to fish oil supplementation mediate any change on the primary outcomes. Apolipoprotein E (ApoE) genotyping was also conducted in order to examine any differential effect of treatment due to carriage of the ApoE-ε4 allele. Blood was taken at the second and third assessment points in order to assess erythrocyte membrane fatty acid composition at each time point. *n*-3 LC PUFA status will be used to assess compliance/uptake post-hoc and we will also assess whether changes in *n*-3 LC PUFA status are associated with any changes on our outcomes. EPA levels in erythrocytes reflect intake over the past month or two, change linearly with dosage (up to 9 g/day), and increase is evident after 3 days of supplementation; EPA and DHA are incorporated equally effectively [42]. Dietary data for current *n*-3 and *n*-6 fatty acid intake was gathered at all time-points, to assess stability of dietary LC PUFA intake over the trial, a food frequency questionnaire (FFQ) was administered as a measure of typical nutrient intake over the preceding one-year period at baseline and at Time 4, and historical seafood consumption was also assessed. Cross-sectional associations between these measures and outcomes will be investigated, and if there are differences between groups at baseline or changes in *n*-3 or overall dietary intake which differ significantly between the active and control groups, then we will control for any potential effects of this on outcomes. Table 1 summarises the data collected at each time point.

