### Statistical Considerations

#### Analysis

Latent growth curve modelling (LGCM) will be the main analysis method used to assess the effect of the intervention. LGCM is an appropriate and rigorous methodology to employ for intervention studies that aim to alter a developmental trajectory and has greater power to detect an effect than models traditionally used in examining interventions, such as ANCOVA or repeated measures ANOVA [69].

Four equally-spaced testing time points were used in this study because, firstly, four time points are required to distinguish between different growth forms (e.g., linear, quadratic) and, secondly, four time points are estimated to give adequate power. The cognitive domains will be modelled as latent variables, providing the cognitive factors prove to be measuring the same construct across time, following the initial planned modelling of the tasks and cognitive factors on baseline data using confirmatory factor analysis (CFA). The main effect of the intervention on each cognitive domain will initially be assessed separately following Muthèn and Curran [69]. The main intervention effect can be tested by modelling the shape of the curve, for the time-points of a construct, for treatment and control groups separately. Both groups are constrained to the same normative growth trajectory, and the treatment slope added to the treatment group. Statistical significance of the mean of the treatment slope indicates a significant main treatment effect. Within this framework, further tests will also examine interaction effects, to determine whether the magnitude of the treatment effect varies as a function of initial cognitive status, and whether other factors, such as carriage of the ApoE-e4 allele, sex, or initial *n*-3 status, moderate the treatment effect. Similar analyses will be undertaken for well-being.

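### Secondary aim 2 lists change in n-3 status, a post-randomisation result of taking the capsules, as a moderator of the treatment effect; baseline status belongs there instead

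*Protocol article*

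**What the plan says.** The protocol article deals with n-3 status in four places.

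- **Methods/Design, secondary aim 2.** The aim is "to determine whether the effect of *n*-3 LC PUFA supplementation on cognitive decline is moderated by presence of the ApoE-ε4 allele, initial cognitive status", and the list goes on to measures of dietary n-3 intake, "including changes in *n*-3 LC PUFA status) or any nutritional, health-related, or psychological factors associated with cognitive outcomes in the elderly". Change in status thus stands in a list of moderators.
- **Compliance.** "Compliance also will be assessed by examination of erythrocyte membrane *n-*3 LC PUFA status and changes in status", with blood taken at each six-monthly assessment.
- **Assessment Administration.** Erythrocyte EPA is said to "change linearly with dosage (up to 9 g/day), and increase is evident after 3 days of supplementation". Status is to be used after the fact to judge compliance and uptake, and "we will also assess whether changes in *n*-3 LC PUFA status are associated with any changes on our outcomes".
- **Analysis.** Besides initial cognitive status, the interaction tests will examine "whether other factors, such as carriage of the ApoE-e4 allele, sex, or initial *n*-3 status, moderate the treatment effect". Every moderator named here is a baseline variable.

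Table 1 shows erythrocyte fatty acid status measured at months 0, 6, 12 and 18, so a baseline value is available.

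**The concern.** A moderator must be a characteristic that treatment cannot alter. The two arms are then comparable at each level of it, and a difference in treatment effect between levels has a causal reading. Change in n-3 status fails that condition: the supplement is meant to cause it, and the trial uses it to tell who took the capsules.

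A large rise means different things in the two arms. In the active arm it marks people who took and absorbed the capsules. In the placebo arm it marks people whose background diet or biology shifted. If the traits behind good adherence or uptake also go with slower decline, the interaction is non-zero even when the supplement does nothing.

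The likely harm is a statement that fish oil slows decline in those whose n-3 status rises most. Readers would take that as dose-response evidence from a randomised trial, although it would rest on a non-randomised comparison.

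**Working it through.** **1. Is change in status affected by treatment?** The article says so itself. It is a compliance marker (Compliance) and dose-responsive (Assessment Administration). The daily supply differs greatly by arm: 1720 + 600 = 2320 mg of DHA plus EPA in the active arm, against 4 × (1.8 + 1.2) = 12 mg in the placebo arm. Change in placebo is therefore mainly background variation.

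**2. Is there a plausible common cause?** The article's section on the ApoE-ε4 allele offers one. It reports that, in a small group of males, non-carriers had the greater rise in EPA and DHA after fish oil. It also reports that carriage is associated with greater risk of decline. Carriage could therefore produce both a smaller rise and faster decline without any effect of the supplement on cognition.

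**3. Do the sections agree?**

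| Section | Role of n-3 status |
|---|---|
| Methods/Design, aim 2 | change is a moderator |
| Analysis | initial status is a moderator |
| Assessment Administration | change is a compliance and uptake marker, and is related to outcome change as an association |

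They do not agree. Only the first row has the fault described here.

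**4. How large could the distortion be?** The article gives no figure to reproduce, so this is a simulation under assumptions. N = 350 comes from the Power section and 1:1 allocation from the randomisation section; 2,000 runs were made per setting. There is no treatment effect. A standardised unmeasured trait has correlation b with the cognitive slope, 0.6 with change in status in the active arm, and 0 with change in placebo (all assumed). The model regresses slope on arm, moderator and their product.

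A formula check: with within-arm variances of 1, the expected interaction coefficient is 0.6b − 0 = 0.6b. Its standard error is about √(1/175 + 1/175) = 0.107. Rejection is approximately Φ(0.6b/0.107 − 1.96) + Φ(−0.6b/0.107 − 1.96).

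| b | 0.6b | Approx. rejection | Simulated, change as moderator | Simulated, baseline moderator |
|---|---|---|---|---|
| 0 | 0 | 5.0% | 5.3% | 5.3% |
| 0.1 | 0.06 | 8.7% | 7.7% | 5.7% |
| 0.2 | 0.12 | 20% | 19% | 4.3% |
| 0.3 | 0.18 | 39% | 40% | 5.3% |
| 0.4 | 0.24 | 61% | 61% | 4.5% |

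Formula and simulation agree closely. The direction is general; the size depends on the assumed correlations.

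**5. The baseline moderators.** Four are named in Analysis. The abstract lists ten constructs in the primary outcome, and domains are first assessed separately. If each moderator is tested in each domain, that is 4 × 10 = 40 tests. With no true interactions, 40 × 0.05 = 2 false positives are expected, whatever the correlation among tests. The chance of at least one is 1 − 0.95^40 = 87% only if the tests are independent. They are not: the baseline speed factors correlate .19 to .70.

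**The case against.** The strongest reply is that this is one parenthesis in a secondary aim. The Analysis section names only baseline moderators, including initial n-3 status, and Assessment Administration handles change separately as a marker of uptake and an association with outcomes. On that view the analysts would never fit the faulty model. Most of this stands: the fault lies in the aim's wording and its conflict with the other two sections. It does not dispose of the point, because aim 2 as written commits the trial to that analysis and the moderator list in Analysis is illustrative, so it does not rule change out.

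Several stronger readings are tempting, and the article does not support them.

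- *All the subgroup findings would be confounded.* ApoE-ε4, sex, initial cognitive status and initial n-3 status precede treatment, so randomisation protects their interactions.
- *Any factor at all may be tested.* The aim is open, but only within nutritional, health-related and psychological factors linked to cognitive outcomes.
- *Collinearity of change with arm inflates the standard error.* That applies to a model with arm and change as additive terms. The interaction compares within-arm slopes, so for a given within-arm spread the mean shift between arms does not enter.
- *A false-positive moderator is nearly certain.* The 87% needs independent tests.
- *The lack of a multiplicity rule is a defect, and ApoE-ε4 should be the sole pre-specified moderator with a Holm correction.* Such rules and the final moderator list may sit in an analysis plan that is not shown. Making ApoE-ε4 the only one would also demote the single interaction the Power section sized: initial status by treatment slope, effect .40, N about 275.

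**Conclusion.** The point holds for change in n-3 status. Aim 2 names a treatment-caused, post-randomisation variable as a moderator. An interaction with it is open to confounding by adherence, health or ApoE-ε4 carriage, and the wording conflicts with the Analysis and Assessment Administration sections.

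The size cannot be fixed from the article. Under the assumptions shown, false-positive rates run from near nominal (7.7%) to 61% as the trait's correlation with cognitive slope goes from 0.1 to 0.4; with no such correlation there is no inflation. These figures show direction, not a forecast.

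The primary analysis is unaffected. The baseline moderators carry only a multiplicity caution, about 2 chance findings expected in 40 tests, and moderators beyond those named should be read as exploratory.

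**What to change.** 1. In secondary aim 2, replace change in n-3 status with baseline erythrocyte n-3 status, matching the Analysis section. The month-0 sample already provides it.
2. Analyse change in status separately and label it exploratory. One route is mediation, which assumes no unmeasured common cause of status change and cognitive slope. The other uses randomised arm as the instrument, which assumes the capsules affect cognition only through n-3 status. State that neither is evidence of effect modification.
3. Apply the same caution to the planned association between change in status and change in outcome: it is an observational comparison.
4. State that moderators other than the four named are exploratory, and report how many interaction tests were run.

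The cost is wording only: no new data, visits or sample size. The trial gives up a dose-response statement framed as moderation, which the design could not support.
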